## **6. STUDY TIME SCHEDULE**

The study is planned to initiate recruitment of families by September 2005 and to be started in January 2006 (LCD diet), with a staggering period of about 12 weeks. The inclusion into the randomized period will start around March, 2006 and stop around June 1, 2006. The active 12 months intervention period will be finished at around June 1, 2007 and the final 24-month follow up visit will complete the study around June 2008. Subsequent analysis, data handling and writing of publications will be performed in years 2008-2010.

## **7. INVESTIGATION AND METHODS**

### **7.1 STUDY VISIT SPECIFIC MEASUREMENTS AND REGISTRATIONS**

The study consists of a total of 26 visits for adults and 18 for children. These are listed below. Screenings will be conducted by research coordinators following a written protocol. Candidates for participation will be scheduled for an initial interview. In the face-to-face interview with the family, all family members will be informed of the nature and requirements of the study, including randomization to treatment conditions. Each family member must give informed written consent (adults and children where appropriate) before any study-related procedures are carried out.

#### **7.1.1. ADULT VISITS**

##### **7.1.1.1 Visit 1, Screening (between week -12 and -9)**

Subjects/families will be allocated a screening number before the screening registrations are carried out. The screening registrations will include:

- Medical history including demographic data and physical examination
- Screening and Eating disorders Questionnaires
- Anthropometric measures: height, weight, etc
- BP
- Fasting glucose will be measured using a finger prick test
- Urine stick test

##### **7.1.1.2 Visit 2, CID 1 (between week -12 and -9)**

This baseline examination will register the following parameters:

- Anthropometric measures including:
  - Weight
  - Waist/hip and sagittal
  - Body composition (DEXA/bioimpedance)
- BP
- Fat biopsy
- Fasting blood samples
- OGTT & VAS scores
- End of day/compliance questionnaire
- Functional questionnaire
- Attitudinal/psychosocial questionnaire
- Food choice questionnaire
- Physical activity scheme
- 3-day diet record including hedonics/hunger questionnaire
- 24-h urine collection

##### **7.1.1.3 Visit 2a (Subgroup a), CID 1a (between week -12 and -9)**

- DLW + urine collection
- BMR
- 7-day diet record
- Pedometer

- Meal test
- VAS scores

#### **7.1.1.4 Visit 3-7 during LCD period, (group meetings >3 families) (week -8, -7, -5, -3 and -1)**

Registrations include:

- Weight
- Dietary instruction
- End of day/compliance questionnaire
- Adverse events & concomitant medication

#### **7.1.1.5 Visit 3b (Subgroup b) during LCD period, (week -8, day 3)**

- Fat biopsy
- Adverse events & concomitant medication

#### **7.1.1.6 Visit 8, randomisation meeting (>3 families) (week 0)**

Registrations include:

- Weight
- Dietary instruction
- End of day/compliance questionnaire
- Adverse events & concomitant medication
- Inclusion/exclusion
- Randomisation

#### **7.1.1.7 Visit 9, CID 2 (individual family meeting) (week 0)**

This family meeting (children participation is preferred but not required) following randomisation will register the following parameters:

- Anthropometric measures including:
  - Weight
  - Waist/hip and sagittal
  - Body composition (DEXA/bioimpedance)
- BP
- Fat biopsy
- Fasting blood samples
- OGTT & VAS scores
- End of day/compliance questionnaire
- Functional questionnaire
- Attitudinal/psychosocial questionnaire
- Food choice questionnaire
- Dietary instruction
- Adverse events & concomitant medication

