#### 1. 8 week LCD dietary period

The energy restricted LCD diet (for adults only) will consist of 800-1000 kcal/d and the target macronutrient composition of the diet will be 15-20% of total energy from fat, 35-40% from protein and 45-50% from carbohydrate. No energy restriction will be imposed for the children in the enrolled families. During this period, subjects will attend approx. 6 group meetings at the Department where their body weight, adverse events (AE) and concomitant medication will be registered and dietary and behavioural instructions will be given.

Before entering intervention period 1, adult subjects visit the Department for CID 2. This will again include anthropometric measurements, BP, blood sample and 24-h urine collection, fat biopsy, OGTT, analysis of body composition (DEXA scan), and completion of lifestyle/behavioural questionnaires. Families where at least one parent achieves a  $>8\%$  weight loss will be randomised to one of the 5 dietary arms.

Subgroup a will complete a 7-day food record and undergo BMR and DLW measurements, have physical activity measured by use of a pedometer and have a meal test.

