## **2. 6 months dietary intervention period 1 (SUPERMARKET period)**

Families in which at least one parent has achieved an 8% loss of initial body weight will be randomised to one of 5 dietary arms (see Table 1), including a control group. Subjects enrolled in the 4 intervention groups will be expected to get most of their foods free of charge in the supermarket for the first 6 months of the intervention. The on-site supermarket has fresh, shelved and frozen products, separated according to the dietary design. All food items will be bar-coded and a dietician will scan the barcodes of all the chosen items to monitor macronutrient composition of the diet and will assist in altering the selection to meet the prescribed macronutrient composition. Each food item scanned will be registered in a database in the shop. The calculated energy content of the chosen groceries will not be made known to the subjects. The control group will be instructed to continue their habitual dietary intake whilst shopping in ordinary food shops (thus their food will not be free).

Families in all intervention groups will receive careful, intensive and regular dietary and behavioural guidance during both intervention periods 1 and 2, although the control group will not receive advice regarding dietary composition. The dietary instruction will include family sessions, where instruction will be given to the whole family, including children. The dietician will advise on weight control and reinforce the diet composition through recipes, cooking advice, and behaviour modification in group (several families) and individual meetings (one family). Subjects will be given oral and written instructions relating to the five intervention groups based on an exchange system. The aim is to reach the required macronutrient composition on a daily basis. Hence, individual meals (breakfast, lunch, dinner) may not necessarily have the designated macronutrient composition. During intervention periods 1 and 2, weight maintenance is attempted, though further weight reduction will be allowed, i.e. in all 5 groups, the diet intervention is carried out with less emphasis on the calorie content of the diet (which is *ad libitum*) or the calorie density of the diet, but with major emphasis on adherence to the diet prescribed. Hence, during both periods 1 and 2 it is the diets' ability to satisfy and to regulate appetite and body weight that will be tested.

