### 4.3 BLINDING

Due to the characteristics of the study design where the dietetic guidance of the study subjects is the inherent intervention in the study, any blinding of the dietician or subjects is not possible. Each dietician will be responsible for guidance of subjects in all five dietary intervention groups.

By any analyses of data obtained prior to study termination, it will be assured that these analyses will not influence the ongoing study and hence the final outcome of the study.

These restrictions will be inferred to exclude any bias introduced by the study personnel.

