### 8.2.4 STATISTICAL METHODS FOR THE PRIMARY OBJECTIVES

Analysis of Covariance (ANACOVA) will be used to compare the main outcome measures in the intervention groups at week 26 and week 52 using the data from CID2 (after weight-loss, adults) or CID1 (children) as covariate.

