### 8.2.5 PRIMARY HYPOTHESIS

The following primary hypothesis can be applied:

H0: The 1o outcome (weight, etc) is equal in the intervention groups at week 26 and week 52, when controlling for the value in CID2 (adults) or CID1 (children).

vs.

H1: The 1o outcome is different in the intervention groups at week 26 and week 52, when controlling for the value in CID2 (adults) or CID1 (children).

The changes in continuously distributed variables from baseline to week 26 and week 52 within treatment groups will be tested with the paired t-test or the Wilcoxon-Signed-rank test, depending on distribution (all tests two-sided).

All categorical variables will be expressed in contingency tables and analyzed using Fisher's exact test. Survival analysis using the Kaplan-Meier plot and the log-rank test will be used to investigate time to subject withdrawal.

All null hypotheses comparing groups assume equality between the treatment groups while the alternative hypotheses assume that there is a difference (two-sided). All within-group null hypotheses assume no change from baseline to week 26 or week 52 while the alternative hypotheses assume that there is a change (two-sided).

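### The adult baseline covariate (CID 2) is scheduled after randomisation in unblinded subjects, so it is not protected from knowledge of allocation; the size of any resulting bias is unknown and may be near zero

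*Protocol*

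**What the plan says.** **Analysis.** Protocol 8.2.4 compares the main outcomes at weeks 26 and 52 by ANACOVA, "using the data from CID2 (after weight-loss, adults) or CID1 (children) as covariate". Section 8.2.5 builds the same conditioning into the primary hypothesis, and 8.2.6 uses the same covariate for the secondary variables at week 26.

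**Visit schedule.** Section 7.1.1.6 puts randomisation at Visit 8, a group meeting in week 0. Its list also contains a weight, dietary instruction and the eligibility check. Section 7.1.1.7 makes CID 2 a separate Visit 9, also in week 0: "This family meeting (children participation is preferred but not required) following randomisation will register the following parameters". Weight, body composition, blood samples, OGTT, appetite scales and several questionnaires are taken there.

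**Design section.** Section 3, under the LCD period, says "Before entering intervention period 1, adult subjects visit the Department for CID 2". After listing the CID 2 measurements it adds that qualifying families "will be randomised to one of the 5 dietary arms". The next item, on intervention period 1, opens with randomisation again: "Families in which at least one parent has achieved an 8% loss of initial body weight will be randomised to one of 5 dietary arms".

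**Blinding.** Section 4.3 states that "any blinding of the dietician or subjects is not possible".

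**The concern.** Adjusting for baseline is safe in a randomised comparison because a value recorded before allocation cannot depend on the arm. Under the visit schedule this protection is lost for adults: the covariate is recorded after allocation, in people who may already know their diet.

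Two things are at stake. Answers to appetite scales and questionnaires can be coloured by knowing the arm, even if nothing physical has changed. And if eating changes between Visits 8 and 9, part of the diet effect enters the baseline and is then adjusted away. The planning difference in Section 8.2.7 is only 1.0 kg, so the covariate should be kept clear of any such effect.

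Section 3 can also be read as putting CID 2 first. Sites working from different sections could therefore record baselines that differ in meaning.

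**Working it through.** The protocol gives no figure on this point, so there is none to reproduce. The check sets the sections side by side and then works out what a shift in the covariate would do.

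**1. Order of events**

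| Source | Order |
|---|---|
| Protocol 7.1.1.6 and 7.1.1.7 | Visit 8: randomisation. Visit 9: CID 2, expressly after it |
| Protocol 3, LCD period | CID 2 described first, randomisation in a later sentence |
| Protocol 3, intervention period 1 | Randomisation described again, as the opening of period 1 |

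The visit schedule is explicit. Section 3 says only that CID 2 precedes intervention period 1; it does not say that CID 2 precedes randomisation. The number of days between Visits 8 and 9 is not given, nor is what subjects eat in between.

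**2. Which measurements are exposed**

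- *Self-reports at CID 2* (appetite scales, functional, psychosocial and food choice questionnaires): exposed as soon as the arm is known.
- *Weight, body composition, blood, OGTT*: exposed only if behaviour or diet changes before Visit 9. CID weights are taken fasting and in underwear (7.2.1), which limits measurement artefact.
- *Children*: not exposed, because their covariate is CID 1, weeks before allocation.

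**3. What a shift would do**

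Let τ be the effect of allocation on week-26 weight, β the covariate slope, and d the mean difference between arms in CID 2 weight caused by allocation.

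Adjusted effect = (difference in week-26 means) − β × (difference in CID 2 means), with expected value τ − βd.

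If CID 2 precedes allocation, d = 0 and the expected value is τ. If it follows, βd is removed. For body weight β is close to 1, because people differ from one another far more than they change.

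A simulation of 1,000,000 subjects checked this. The effect (1.0 kg lower weight) and the residual SD (2.5 kg) are the planning values of Section 8.2.7. Mean weight 90 kg, between-person SD 15 kg and covariate noise SD 0.5 kg are assumptions. The fitted slope was about 1.0.

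| Assumed shift at CID 2, same direction as the effect (kg) | Adjusted effect (kg) |
|---|---|
| 0 | −1.00 |
| 0.1 | −0.91 |
| 0.2 | −0.80 |
| 0.3 | −0.70 |
| 0.5 | −0.50 |

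These shifts test the algebra; they are not estimates of what would happen in this trial. By the same formula a shift in the opposite direction would inflate the effect: with τ = −1.0, β = 1 and d = +0.2, the result is −1.0 − 0.2 = −1.2 kg.

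**The case against.** **The sections can be reconciled.** A reader might infer a flat contradiction, with Section 3 ordering CID 2 before randomisation. The text does not go that far. Section 3 uses the same form of words for CID 3 and period 2, where it marks the boundary between diet periods. Randomising at Visit 8, measuring CID 2 at Visit 9 and then starting the diet satisfies every sentence. This stands: only the order of sentences in Section 3 points the other way. But the reconciled reading still leaves the covariate after allocation and unblinded.

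**No exposure before CID 2 is documented.** A reader might infer that subjects are already eating the assigned diet, or have had arm-specific teaching, when CID 2 is measured. The assigned diet and the shop belong to period 1. Instruction at Visit 8 is listed above randomisation, and the same item appears at the LCD visits; at Visit 9 it is listed after the measurements. This also stands, and it is why no share of the planned effect can be said to be lost.

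**Early withdrawal is not hidden.** A reader might infer that families who leave on learning their arm would go unseen. They would not: drop-out rate is a main outcome (8.2.2), time to withdrawal has a Kaplan-Meier and log-rank analysis (8.2.5), and date and reason are recorded at discontinuation (5.3). Such subjects leave the primary comparison because it is restricted to completers (8.2.4), and moving CID 2 would not bring them back.

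What the objections do not answer is that a primary-analysis covariate is scheduled after allocation when it could be taken before.

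**Conclusion.** The point holds in a limited form. By the visit schedule, the adult covariate of the primary analysis follows randomisation in unblinded subjects and is not protected from knowledge of allocation. Section 3 leaves the order open and, by its sequence, suggests the opposite.

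Self-reported measures are the most exposed. For weight and body composition, the bias depends on whether diet changes between two week-0 visits. The protocol does not state this, so neither size nor direction can be derived, and the bias may be near zero. What can be said, assuming a covariate slope near 1, is that each kilogram of differential shift before CID 2 would move the adjusted effect by about one kilogram. Children's analyses are not affected.

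**What to change.** Reconcile Section 3 with Sections 7.1.1.6 and 7.1.1.7 and state one order:

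1. Check the weight-loss criterion at Visit 8, where a weight and the eligibility check are already listed.
2. Complete all CID 2 measurements at Visit 9.
3. Generate and disclose the allocation, and give arm-specific instruction, only after that, for example at the end of Visit 9.

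Checking the criterion first avoids CID 2 biopsies and OGTTs in families that are then not randomised. The cost is small: disclosure moves from the group meeting to the individual family meeting.

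If CID 2 cannot be completed before allocation for some families, a Visit 8 weight taken before allocation could serve as a fallback covariate for body weight only. It would have to be taken under CID conditions, since 7.2.1 otherwise asks only for no coat and shoes. It cannot stand in for body composition, blood or OGTT, none of which is listed at Visit 8.

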#### **7.1.1.8 Visit 9a (Subgroup a), CID 2a (week 0)**

- DLW + urine collection
- BMR

- 7-day diet record
- Pedometer
- Meal test & VAS

#### **7.1.1.9 Visit 10, individual family meeting (week 2)**

Registrations include:

- Weight
- Dietary instruction
- End of day/compliance questionnaire
- Adverse events & concomitant medication
- 3-day diet record including hedonics/hunger questionnaire

#### **7.1.1.10 Visit 11, individual family meeting (week 4)**

Registrations include:

- Weight
- Dietary instruction
- End of day/compliance questionnaire
- Adverse events & concomitant medication
- 24-h urine collection

#### **7.1.1.11 Visit 12 & 13, individual family meeting (week 6)**

Registrations include:

- Weight
- Dietary instruction
- End of day/compliance questionnaire
- Adverse events & concomitant medication

#### **7.1.1.12 Visit 14, (group meetings >3 families) (week 10)**

Registrations include:

- Weight
- Dietary instruction
- End of day/compliance questionnaire
- Adverse events & concomitant medication

#### **7.1.1.13 Visit 15, (group meetings >3 families) (week 14)**

Registrations include:

- Weight
- Dietary instruction
- End of day/compliance questionnaire
- Adverse events & concomitant medication
- 24-h urine collection

#### **7.1.1.14 Visit 16 & 17, (group meetings >3 families) (week 18 & 22)**

Registrations include:

- Weight

- Dietary instruction
- End of day/compliance questionnaire
- Adverse events & concomitant medication

#### **7.1.1.15 Visit 18, CID 3, end of intervention period 1 (week 26)**

This family meeting will register the following parameters:

- Anthropometric measures including:
  - Weight
  - Waist/hip and sagittal
  - Body composition (DEXA/bioimpedance)
- BP
- Fat biopsy
- Fasting blood samples
- OGTT & VAS scores
- End of day/compliance questionnaire
- Functional questionnaire
- Attitudinal/psychosocial questionnaire
- Food choice questionnaire
- Dietary instruction
- Adverse events & concomitant medication
- 3-day diet record including hedonics/hunger questionnaire
- 24-h urine collection

#### **7.1.1.16 Visit 18a (Subgroup a), CID 3a (week 26)**

- DLW + urine collection
- BMR
- 7-day diet record
- Pedometer

#### **7.1.1.17 Visit 19-24, family meeting (week 28, 32, 36, 40, 44 & 48)**

Registrations include:

- Weight
- Dietary instruction
- End of day/compliance questionnaire
- Adverse events & concomitant medication

#### **7.1.1.18 Visit 25, CID 4, end of intervention period 2 (week 52)**

This family meeting will register the following parameters:

- Anthropometric measures including:
  - Weight
  - Waist/hip and sagittal
  - Body composition (DEXA/bioimpedance)
- BP
- Fasting blood samples
- OGTT & VAS scores
- Dietary instruction

- Adverse events & concomitant medication
- 3-day diet record
- 24-h urine collection

#### **7.1.1.19 Visit 26, family follow-up meeting (week 104)**

Registrations include:

- Weight
- Waist/hip and sagittal
- Dietary instruction (adherence)
- BP
- Adverse events & concomitant medication

#### **7.1.1.20 Early termination**

The registrations include (listed by priority):

- Date & reason for discontinuation
- Adverse events & concomitant medication
- Physical examination including BP (only if early termination is due to adverse event)
- Weight
- Body composition (DEXA-scanning/bioimpedance)
- Blood samples
- End of day/compliance Questionnaire
- RTD4 Questionnaires?
- Waist/hip and sagittal measurement
- Nutritional counselling

There will be a maximum volume of 110 ml blood taken on each CID day and max. 2g adipose tissue.

BIDR questionnaire

### **7.1.2. VISITS FOR CHILDREN (NB: No questionnaires are completed by children)**

#### **7.1.2.1 Visit 1, Screening (between week -12 and -9) (all children)**

Subjects/families will be allocated a screening number before the screening registrations are carried out. The screening registrations will include:

- Medical history including demographic data and physical examination
- Anthropometric measures: height, weight, etc

#### **7.1.2.2 Visit 2, CID 1 (between week -12 and -9)**

This baseline examination will register the following parameters:

- Anthropometric measures including:
  - Weight (all children)
  - Height (all children)
  - Waist/hip (overweight children only)
  - Body composition (DEXA/bioimpedance) (overweight children aged >12 years only)
- Physical activity scheme

- 3-day diet record (overweight children only)
- Fasting blood samples (all children)
- BP (overweight children only)

#### **7.1.2.3 Visit 3, randomisation family meeting (week 0)**

*NB: Children participation preferred but optional*

Registrations include (all children):

- Weight
- Height
- Dietary instruction
- Adverse events & concomitant medication

#### **7.1.2.4 Visit 4, family meeting (week 2)**

Registrations include (all children):

- Weight
- Height
- Dietary instruction
- Adverse events & concomitant medication

#### **7.1.2.5 Visit 4, CID 2 & family meeting (week 4)**

This family meeting will register the following parameters:

- Anthropometric measures including:
  - Weight (all children)
  - Height (all children)
  - Waist/hip (overweight children only)
  - Body composition (DEXA/bioimpedance) (overweight children aged >12 years only)
- Fasting blood samples (all children)
- Dietary instruction (all children)
- BP (overweight children only)
- Adverse events & concomitant medication (all children)
- 3-day diet record (overweight children only)

#### **7.1.2.6 Visit 5 & 6, family meeting (week 6 & 10)**

Registrations include (all children):

- Weight
- Height
- Dietary instruction
- Adverse events & concomitant medication

#### **7.1.2.7 Visit 7, family meeting (week 14)**

Registrations include (all children):

- Weight
- Height
- Dietary instruction
- Adverse events & concomitant medication

#### **7.1.2.8 Visit 8 & 9, family meeting (week 18 & 22)**

Registrations include (all children):

- Weight
- Height
- Dietary instruction
- Adverse events & concomitant medication

#### **7.1.2.9 Visit 10, CID 3, end of intervention period 1 (week 26)**

This family meeting will register the following parameters:

- Anthropometric measures including:
  - Weight (all children)
  - Height (all children)
  - Waist/hip (overweight children only)
  - Body composition (DEXA/bioimpedance) (overweight children aged >12 years only)
- Fasting blood samples (all children)
- Dietary instruction (all children)
- Adverse events & concomitant medication (all children)
- BP (overweight children only)
- 3-day diet record (overweight children only)

